### Randomization, Allocation Concealment, and Blinding

Participants will be randomized using a computer-generated permuted block design with variable block sizes of 3 and 6. To ensure structural balance, randomization will be stratified within the REDCap module into 2 parallel sequences: stratum 1 (active ulcer present: Wagner grade ≤2) and stratum 2 (no active ulcer). Upon coordinator registration, the participant’s clinical ulcer status will automatically determine the next sequential allocation exclusively from the corresponding stratum block. Neither participants nor surgeons will be blinded due to the nature of the intervention; however, outcome assessors and statisticians will remain blinded to group allocation. To minimize the risk of unblinding, standardized dressings will be used across groups, and independent assessors will conduct outcome evaluations. The enrollment, randomization, intervention, and follow-up processes are summarized in Figure 1 and Table 1.

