#### Follow-Up Assessments

At 6 months, participants will undergo repeat assessments, including Sudoscan, HRV, QST, MNSI, and DN4, with testing supported by self-payment arrangements. Additionally, any changes in time-varying covariates, such as concomitant treatments (eg, adjustments to neuropathic pain medications or glycemic control agents), will be systematically reviewed and recorded. At 12 months, similar assessments (Sudoscan, HRV, QST, MNSI, and DN4) and IENFD evaluation will be performed, with reimbursement provided under the National Health Insurance framework. These follow-up evaluations are intended to capture both the primary end point at 6 months and the durability of outcomes at 12 months.

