### Statistical Analysis

A total sample size of 60 randomized participants (LVB n=40; SOC n=20) provides 80% power (*α*=0.05) to detect a conservative between-group effect size of Cohen *d*=0.70 for the primary end point. This target randomized sample size accounts for an anticipated 15% dropout and missing data rate across both groups to ensure that the study remains adequately powered for the final analysis. This calculation was performed using G*Power (version 3.1.9.7) based on a 2-sample *t* test framework to ensure robust power for the subsequent longitudinal analysis. All statistical analyses will be performed using SPSS (version 28.0; IBM Corp). The primary analysis will follow the intention-to-treat principle, with per-protocol analyses conducted as sensitivity checks. The primary end point—jointly defined as the changes in DN4 and MNSI at 6 and 12 months—will be analyzed using a mixed-effects model for repeated measures (MMRM). Continuous secondary end points, including ESC values, SSR latencies or amplitudes, HRV parameters, and QST thresholds, will be analyzed using identical, parallel MMRM frameworks to control for baseline values and time-varying covariates. Exploratory biomarker analyses will use analysis of covariance or mixed models, with multiple testing controlled by the Benjamini-Hochberg false discovery rate. Missing data will be assumed to be missing at random, with MMRM inherently accommodating missingness and multiple imputation using Multiple Imputation by Chained Equations applied for sensitivity analyses. To ensure stability, given the small control group (n=20), Multiple Imputation by Chained Equations will use a restricted set of covariates. An anticipated dropout and missing data rate of 15% is expected across both groups. Prespecified exploratory, hypothesis-generating subgroup analyses will evaluate outcomes by ulcer status, baseline DPN stage, hemoglobin A_1c_ tertiles, dyslipidemia, and chronic kidney disease. Interim analyses will be restricted to safety reviews by the DSMB after approximately 20 and 40 participants, with no efficacy-based stopping rules.

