Several limitations must be acknowledged. The single-center design may constrain generalizability, and the inability to blind participants and surgeons introduces a risk of performance bias, although this limitation is mitigated by the use of objective, assessor-blinded measures such as ESC and NCS. The heterogeneity of DPN phenotypes, including the broad age range (20-80 years) included in our eligibility criteria, presents additional challenges in interpreting subgroup responses; however, our statistical model adjusts for age and diabetes duration to mitigate this issue. Although the sample size is adequately powered for the primary end point, it may be underpowered to detect smaller effects across secondary and exploratory outcomes. The small sample size, particularly in the SOC control group (n=20), poses a significant constraint relative to the planned complex multivariable MMRM analyses and increases the risk of unstable estimates. Future research should include multicenter replication to validate findings, cost-effectiveness analyses to assess feasibility in routine practice, and refinement of indications such as early autonomic DPN or refractory ulcer phenotypes. Comparative effectiveness studies, including evaluation alongside emerging pharmacologic agents such as glucagon-like peptide-1 receptor agonists, are also warranted. Taken together, this trial has the potential to establish LVB as a paradigm-shifting intervention that redefines the therapeutic landscape of DPN.

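### The MMRM wording adjusts for drug changes made after randomisation, which can bias the arm effect in either direction and departs from the intention-to-treat effect the plan promises

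*Protocol article*

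**What the plan says.** All references are to the protocol article.

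- **Statistical Analysis, primary end point.** The changes in DN4 and MNSI at 6 and 12 months "will be analyzed using a mixed-effects model for repeated measures (MMRM"). No covariates are named in that sentence.
- **Statistical Analysis, secondary end points.** The next sentence covers ESC, SSR, HRV and QST and plans "identical, parallel MMRM frameworks to control for baseline values and time-varying covariates".
- **Statistical Analysis, principle.** "The primary analysis will follow the intention-to-treat principle".
- **Follow-Up Assessments.** At 6 months the site will review and record "any changes in time-varying covariates, such as concomitant treatments (eg, adjustments to neuropathic pain medications or glycemic control agents").
- **Discussion, limitations paragraph.** On heterogeneity and the wide age range: "our statistical model adjusts for age and diabetes duration to mitigate this issue".
- **Randomization, Allocation Concealment, and Blinding.** The strata are "stratum 1 (active ulcer present: Wagner grade ≤2) and stratum 2 (no active ulcer"), and neither participants nor surgeons are blinded. In the analysis text, ulcer status appears only as an exploratory factor: "subgroup analyses will evaluate outcomes by ulcer status, baseline DPN stage".

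**The concern.** Read together, the two sections that use the term time-varying covariates put variables measured after randomisation into the efficacy models. Pain control and glycemic management belong to standard care in both arms and can be changed at any time during follow-up. In an open-label trial, such changes can respond to knowledge of the arm and to symptoms that the surgery may have altered.

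Conditioning on such a variable does two things. If the drug change itself moves the outcome, part of the treatment's total effect passes through it, and adjustment takes that part out. If unmeasured severity drives both the drug change and the outcome, adjustment compares participants in the two arms who are no longer alike, and this creates a difference that randomisation had removed. Either way the arm coefficient is not the effect of being assigned to LVB, which is what an intention-to-treat analysis estimates.

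The problem is sharpest for DN4, where a pain-related outcome would be adjusted for changes in pain treatment. If the adjustment applies only to the secondary end points, it still covers ESC, one of the blinded measures that the limitations paragraph relies on to offset the open-label design.

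**Working it through.** **1. Which models are affected.** The quoted sentence governs the continuous secondary end points. It directly follows the primary MMRM sentence and calls the secondary frameworks identical and parallel. The nearest thing they can be identical to is the primary model. That is the natural reading but an inference.

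**2. When the covariates arise.** The examples are adjustments to pain drugs and glycemic agents, reviewed at the 6-month visit. They arise after randomisation, under known allocation.

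**3. How far the coefficient can move.** The documents give no rate of drug change and no drug effect, so every input below is assumed. All cases use 2:1 allocation, one follow-up measurement and least squares in very large samples, so they show bias and not sampling error. Negative values mean benefit. Units are SDs, of latent pain in (a) and (b) and of the outcome's underlying variation in (c) and (d).

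(a) *Drug change as a pure mediator.* Direct effect −0.70, drug effect −0.4, drug change in 25% (LVB) vs 42% (SOC).
- Total effect = direct effect + drug effect × (p_LVB − p_SOC) = −0.70 + (−0.4)(0.25 − 0.42) = −0.70 + 0.068 = −0.632.
- Adjusted effect = −0.70.
- Ratio 0.70/0.632 = 1.11, so adjustment makes the LVB effect about 11% **larger**.

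(b) *Drug change driven by current pain.* Pain = N(0,1) − 0.7 × arm; P(escalation) = logistic(1.5 × (pain − 0.3)); outcome = pain − 0.4 × escalation + noise. Escalation is again about 25% vs 42%.
- Without baseline score: −0.635 unadjusted, −0.520 adjusted. Shrinkage (0.635 − 0.520)/0.635 = 18%.
- With a baseline score correlated 0.7 with the latent pain: −0.637 and −0.598. Shrinkage (0.637 − 0.598)/0.637 = 6%.
- Without the baseline score, the fitted escalation coefficient is +0.69 although the simulated drug effect is −0.4. Escalation is acting as a marker of severity.

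(c) *No true effect.* Latent severity drives both drug change and outcome; drug change also depends on arm; the drug does nothing.

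| Drug change, LVB vs SOC | Unadjusted | Adjusted |
|---|---|---|
| 21% vs 34% | 0.00 | +0.07 |
| 11% vs 34% | 0.00 | +0.12 |

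A spurious difference appears, here against LVB. If escalation were more frequent under LVB, the sign would reverse.

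(d) *Drug change unrelated to arm* (34% in both arms, drug effect −0.3): −0.71 unadjusted, −0.71 adjusted. No bias.

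**4. Scale.** With 40 and 20 participants, the standard error of an unadjusted difference is √(1/40 + 1/20) = 0.27 SD. A shift of 0.12 SD is 0.12/0.27 = 0.44 of that, and 0.12/0.70 = 17% of the planning effect. Unlike sampling error, it would not shrink with more participants.

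**5. Covariates named.** Statistical Analysis names baseline values and time-varying covariates. The limitations paragraph names age and diabetes duration. The two statements differ, and neither mentions the ulcer stratum.

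**The case against.** The sentence is about secondary end points, and the word identical could mean alike across those end points instead of the same as the primary model. The Follow-Up Assessments section says drug changes are recorded and offers them as examples, not as a closed covariate list. ESC, SSR, HRV and QST are physiological or threshold tests, so the link through pain is weaker there than for DN4. If drug changes do not differ by arm, adjustment does no harm. All of this stands. It limits what can be asserted about the primary model and about size. It does not remove the problem, because the article uses the same term in both places and states that the models control for these covariates. This is a stated choice, not an omission.

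Three stronger readings are tempting and not supported.

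- *The adjustment will shrink the LVB effect because the model credits the drug.* Case (a) shows that when the drug truly carries part of the effect, adjustment enlarges the arm effect. The shrinkage in case (b) arises because escalation marks severity, and the fitted model makes the drug look harmful.
- *The loss in this trial is 18%.* That figure comes from assumed inputs without a baseline score, which the plan does include; with one it is about 6%.
- *Leaving the ulcer stratum out is an error.* The article gives no complete covariate list and does not exclude the stratum. A condensed article may leave this to the full protocol or analysis plan. Omitting a stratification factor mainly costs precision.

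**Conclusion.** As written, the plan controls for drug changes that occur after randomisation. It does so explicitly for the continuous secondary end points and, on the most natural reading, for DN4 and MNSI as well. That can bias the arm effect and conflicts with the intention-to-treat principle stated in the same section. Bias requires drug changes to depend on arm or on symptoms affected by treatment, which is plausible without blinding.

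Direction and size in this trial are unknown. The illustrations range from 6–18% shrinkage to about 11% inflation, with a spurious difference of about 0.1 SD under no effect and no bias when drug change is unrelated to arm. These show what is possible and are not estimates for this trial. The point rests on the wording, not on any of these figures. It should be corrected before any outcome data exist; the article reports 3 participants enrolled and no outcome data.

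**What to change.** In Statistical Analysis, replace the reference to baseline values and time-varying covariates with baseline covariates only, and state that this applies to both the primary and the secondary MMRMs. A suitable list is the baseline score and the ulcer randomisation stratum, plus age and diabetes duration as the limitations paragraph already names. Make the two sections give the same list. Adding the stratum brings the model into line with the randomisation for a minor gain in precision.

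State that the effect is estimated regardless of changes in concomitant drugs. Continue to record those changes, tabulate them by arm and visit, and present any model that includes them as a labelled supplementary analysis.

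The cost is a change of analysis wording. Recruitment, visits, data collection and sample size are unaffected.

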### Schedule of Assessments

#### Baseline Assessments

At trial inclusion, demographic and clinical variables will be collected, including age, sex, and relevant past medical history (including diabetes mellitus, hypertension, chronic kidney disease, and diabetic retinopathy) from the electronic medical record. Physical examination parameters will include BMI and waist circumference. Laboratory assessments will comprise fasting plasma glucose, glycated hemoglobin (hemoglobin A_1c_), triglycerides, blood urea nitrogen, and serum creatinine. Baseline severity of diabetic neuropathy will be evaluated through NCS, QST, HRV, ESC (measured using Sudoscan, if not performed within the preceding 3 months), and symptom scoring with the MNSI and DN4. Ulcer status will be documented and photographed when present, and IENFD from ulcer biopsy specimens will be evaluated by a neurologist.

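### The exploratory HbA1c subgroup analysis is fixed as tertiles of a measured number; a continuous interaction would use the same data better at almost no cost (minor)

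*Protocol article*

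**What the plan says.** The Statistical Analysis section of the protocol article prespecifies subgroup analyses and labels them exploratory and hypothesis-generating. The factors are ulcer status and then "baseline DPN stage, hemoglobin A_1c_ tertiles, dyslipidemia, and chronic kidney disease". HbA1c is the only one given a cut rule. No analysis with HbA1c as a continuous effect modifier appears in the article, and the section does not say whether subgroups will be compared by an interaction test or only described one by one.

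The Baseline Assessments section collects HbA1c as a laboratory value, alongside other blood measures: "fasting plasma glucose, glycated hemoglobin (hemoglobin A_1c_), triglycerides". The numeric value should therefore be available for participants generally.

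On size, the Statistical Analysis section gives "A total sample size of 60 randomized participants (LVB n=40; SOC n=20") and adds: "This target randomized sample size accounts for an anticipated 15% dropout and missing data rate across both groups". Randomization is stratified by ulcer status only, so nothing balances the arms within HbA1c tertiles.

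**The concern.** Cutting a measured variable into thirds treats everyone within a third as alike and places the boundaries wherever the sample happens to fall. With 20 controls, each third keeps about seven. Two things are at stake. Separate tertile estimates will be very imprecise, and a test of whether the LVB effect varies with glycemic control will usually have less power than it could have from the same data. Sample-dependent cut points are also hard to carry over to the multicenter replication that the Discussion calls for.

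This is a choice that the article makes, not a detail left open. It names tertiles and calls the analyses prespecified.

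**Working it through.** **The plan's own figure.** The article gives no power or precision for the HbA1c analysis, so there is none to reproduce. Its 80% power at d = 0.70 concerns the primary end point and does not enter this check. (A two-sample t test at 40:20 gives 71% two-sided and 81% one-sided, before dropout. That is a separate matter.)

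**Inputs from the Statistical Analysis section.** LVB 40, SOC 20, dropout 15% in both arms, hence 40 × 0.85 = 34 and 20 × 0.85 = 17 completers.

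**Inputs assumed here, because the article gives none.** Residual SD of 1, normally distributed HbA1c, a linear interaction, and slopes (change in treatment effect, in outcome SD, per SD of HbA1c) of 0.35, 0.5 and 0.8.

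**Step 1: numbers per tertile.**
- Randomized: 40/3 = 13.3 LVB and 20/3 = 6.7 SOC.
- Completers: 34/3 = 11.3 LVB and 17/3 = 5.7 SOC.
- These are averages. With cut points taken from the whole sample of 60, simulation puts the control count in the sparsest tertile at 4.9 on average, with a 5th percentile of 3.

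**Step 2: precision within one tertile, unadjusted.** SE = sqrt(1/n_LVB + 1/n_SOC), in SD units. Half-width = t(0.975, df) × SE.
- Randomized: sqrt(1/13.3 + 1/6.7) = 0.474; df 18, t = 2.10; half-width 1.00 SD.
- After dropout: sqrt(1/11.3 + 1/5.7) = 0.514; df 15, t = 2.13; half-width 1.10 SD.

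Both exceed the 0.70 SD that the whole trial is designed to detect. With 13 against 7, two-sided power for d = 0.70 is 29%, and the effect detectable with 80% power is d = 1.39.

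**Step 3: power of the interaction at 34:17.** Simulated in a linear model, 5% level, with three codings of the same HbA1c values. Ranges show the spread over independent runs.

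| Assumed slope | Continuous, 1 df | Tertile trend score, 1 df | Tertiles, 2 df |
|---|---|---|---|
| 0.8 | 69% | 58% | 44–46% |
| 0.5 | 35–36% | 27–29% | 20–23% |
| 0.35 | 19–20% | 16–17% | 12–13% |

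Type I error was about 5% for all three. For a normal covariate, the asymptotic efficiency of a tertile score relative to the continuous value is 0.79.

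**Step 4: departures from the assumptions (40:20, slope 0.85).**
- Skewed HbA1c, linear interaction: 79% continuous, 67% trend score, 55% on 2 df. The loss remains.
- Effect differs only in the top tertile, scaled to the same SD: 54% continuous, 69% trend score, 74% on 2 df. The ranking reverses.
- U-shaped effect: 9% continuous, 4% trend score, 13% on 2 df. No form is useful.

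**The case against.** The strongest reply is that little depends on this. The article labels the subgroup analyses exploratory. Its limitations paragraph also admits difficulty in interpreting subgroup responses, possible underpowering of secondary and exploratory outcomes, and the constraint of 20 controls. No decision rule or confirmatory claim uses the tertiles. All of that stands and sets the weight at minor.

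The size of the loss is also open to challenge. The article names no test, so the 2-df comparison is a worst case. Against a trend score the loss at slope 0.8 is about 11 points (69% to 58%), not 23 to 25. A slope of 0.8 is itself very large: it moves the treatment effect by 2 × 0.8 = 1.6 SD between −1 and +1 SD of HbA1c, more than twice the planned 0.70. At 0.5 the continuous test has about 35% power and would still miss a real interaction roughly two times in three. The main limit is sample size, not coding. Under a threshold effect tertiles win, and a linearity check with 17 controls is weak. The half-widths come from an unadjusted single-time comparison, and the planned repeated-measures model with baseline adjustment could narrow them. These points stand too.

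What survives is comparative. If the effect varies smoothly with HbA1c, every tertile coding simulated does worse than the measured value, on data already collected. The article states no threshold hypothesis that would favor thirds.

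A reader might also infer that this subgroup analysis is meant to guide phenotype-directed treatment, which would raise the stakes. The documents do not support that. The abstract's conclusion ties such algorithms to LVB being effective overall, and the Discussion ties them to gains in small-fiber function and ulcer healing. It leaves refinement of indications to future research, with early autonomic neuropathy and refractory ulcers as its examples. None of these places mentions HbA1c.

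**Conclusion.** The point holds as a cheap improvement of minor weight. The article fixes a less informative form for a variable that it measures as a number. The within-tertile half-width of about 1.0 to 1.1 SD follows from the stated sample size and dropout for an unadjusted comparison. The power loss is conditional: with a linear interaction and 34:17 completers, about 6 to 11 points against a trend score and 12 to 25 points against a 2-df test, for slopes of 0.5 to 0.8. Those slopes, the linearity and the choice of test are assumptions made here. The exact loss cannot be fixed from the document, and its sign can change under a threshold effect.

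It would be too strong to say that the continuous form rescues the analysis, or that tertiles will make the trial miss an effect it would otherwise find. This analysis is underpowered either way, and no primary conclusion is affected.

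**What to change.** In the Statistical Analysis section, replace the HbA1c tertile entry with a treatment-by-baseline-HbA1c interaction, HbA1c continuous, in the planned MMRM. Report the estimated treatment effect with its 95% confidence interval at a few HbA1c values chosen in advance. Keep tertile summaries for display and as a rough check on linearity, and keep the exploratory label.

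The cost is a wording change with no new data and no new visits. The price is reliance on an approximately linear interaction, which should be stated, with the note that a threshold effect could be shown less well. The article reports three participants enrolled and no outcome data available, so the change can be made now without appearing data-driven.

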### Data Management

The study data recorded using electronic case report forms will be retained for at least 5 to 10 years. Risk-based monitoring will be performed, with 100% source data verification for the primary end point and informed consent. LVB is considered a low-risk microsurgical procedure, and participant safety will be overseen by an independent DSMB.

## Discussion

This trial evaluates LVB as a mechanism-based adjunctive therapy for DPN. Regarding our principal findings, we anticipate that supermicrosurgical restoration of lymphatic-venous drainage will significantly improve small-fiber and autonomic function—reduce neuropathic pain and increase ESC—and accelerate epithelialization in participants with active ulcers. In comparison to prior work, this localized surgical approach addresses a critical gap left by conventional pharmacotherapies that merely treat symptoms without modifying the underlying pathophysiology. This protocol is the first clinical trial evaluating LVB specifically for DPN, paralleling successes observed in populations with lymphedema and venous ulcers. The trial’s major strengths include its randomized, assessor-blinded design and the integration of biomarker and histological substudies. Finally, our dissemination plan ensures that these findings will be shared through peer-reviewed medical literature and international congresses to inform future precision care algorithms.

Reduced IENFD is a critical histopathological marker of diabetic neuropathy that significantly contributes to the pathogenesis and impaired healing of diabetic foot ulcers. The progressive loss of these small nerve fibers, driven by metabolic and microvascular injury, leads to diminished protective sensation and disruption of neurotrophic and neurovascular support. This lack of sensory feedback allows minor foot injuries to go unnoticed, while the absence of key neuropeptides, such as calcitonin gene-related peptide and substance P, impairs local blood flow and tissue regeneration. The combination of compromised sensation and a blunted healing response creates a vicious cycle that contributes to the chronicity and high morbidity of these ulcers [25,26]. Therefore, the assessment of IENFD, often through skin biopsies, serves as a valuable diagnostic and prognostic tool by offering insight into the neural contributions to ulcer pathogenesis and serving as a sensitive end point for evaluating therapeutic efficacy.

Diabetic autonomic neuropathy is a key factor in the development and poor healing of diabetic foot ulcers. Assessments such as HRV and SSR are essential for evaluating this condition. A decrease in HRV indicates parasympathetic dysfunction, increasing cardiovascular risk, while an absent or reduced SSR indicates sympathetic nerve failure, causing dry, cracked skin. This dual impairment—loss of protective sensation from somatic neuropathy and compromised skin integrity from autonomic dysfunction—creates a cycle in which minor injuries go unnoticed, and the body’s natural healing processes are hindered, leading to chronic, nonhealing ulcers [27,28]. Therefore, a comprehensive assessment of both somatic and autonomic neuropathy is vital for effective management and risk stratification in patients with diabetic foot ulcers. We will evaluate the effectiveness of LVB in alleviating diabetic autonomic neuropathy.

The strengths of this study include its randomized, assessor-blinded design, the incorporation of objective autonomic and electrophysiologic end points, and the integration of biomarker and histological substudies to provide mechanistic insight. The inclusion of ulcer-related outcomes further enhances the clinical relevance of the study, as foot ulcers remain a major cause of morbidity and amputation in DPN. Positive findings, particularly improvements in small-fiber function and ulcer healing, could inform future treatment algorithms tailored to specific DPN phenotypes, thereby advancing precision care in diabetic neuropathy.

Several limitations must be acknowledged. The single-center design may constrain generalizability, and the inability to blind participants and surgeons introduces a risk of performance bias, although this limitation is mitigated by the use of objective, assessor-blinded measures such as ESC and NCS. The heterogeneity of DPN phenotypes, including the broad age range (20-80 years) included in our eligibility criteria, presents additional challenges in interpreting subgroup responses; however, our statistical model adjusts for age and diabetes duration to mitigate this issue. Although the sample size is adequately powered for the primary end point, it may be underpowered to detect smaller effects across secondary and exploratory outcomes. The small sample size, particularly in the SOC control group (n=20), poses a significant constraint relative to the planned complex multivariable MMRM analyses and increases the risk of unstable estimates. Future research should include multicenter replication to validate findings, cost-effectiveness analyses to assess feasibility in routine practice, and refinement of indications such as early autonomic DPN or refractory ulcer phenotypes. Comparative effectiveness studies, including evaluation alongside emerging pharmacologic agents such as glucagon-like peptide-1 receptor agonists, are also warranted. Taken together, this trial has the potential to establish LVB as a paradigm-shifting intervention that redefines the therapeutic landscape of DPN.
